### Schedule of evaluations/Estimated timelines

This study consists of three phases: (1) the screening phase, (2) the treatment phase and (3) the follow-up phase (Table 1).

**Table 1 Tab1:** Clinical treatment plan

	Inclusion into study	Screening	Assignment to treatment group	Treatment phase	EOT	6 weeks after EOT	12 weeks after EOT = End of study
Time		Day −15 –day 0	0 (visit 0)	Days 1–90 (visits 1–3) −3d to +3d	Visit 3	Day 129– day 135 (visit 5) −3d to +3d	Day 171– day 177 (visit 6) −3d to +3d
Informed consent	x						
Demographics		X					
Medical history concomitant medication		X		x	X	x	X
Physical exam, vital signs, weight		X	x	x	X	x	X
ECG		X					
ECOG performance status and QOL assessment		X	x	x	X	x	X
Blood tests including pregnancy test		X	x	x	X	x	X
EGD with biopsies			x		X	x	X
	Inclusion into study	Screening	Assignment to treatment group	Treatment phase	EOT	6 weeks after EOT	12 weeks after EOT = End of study
Time		Day −15–day 0	0 (visit 0)	Days 1–90 (visits 1–3) −3d to +3d	Visit 3	Day 129– day 135 (visit 5) −3d to +3d	Day 171– day 177 (visit 6) −3d to +3d
*H. pylori* serology			x				
Stool samples			x	x	x	x	x
Rapid urease test			x				
Assessment of neurocognitive function (NCT-A, CFF, VEP, EEG)		X		Days 1–28 weekly, then every 4 weeks	>x	x	x

*CFF* critical flicker frequency, *ECG* electrocardiogram *ECOG* Eastern Cooperative Oncology group, *EEG* electroencephalogram, *EGD* esophagogastroduodenoscopy, *EOT* end of treatment, *NCT-A* number-connection test A, *QOL* quality of life, *VEP* visual evoked potentials

### Recruitment

Patients will be recruited in the hospital department where they are treated for their primary disease. This will usually be the Department of Gastroenterology, Hepatology and Infectious Diseases of the University of Magdeburg, Germany. Patients will be informed by the investigator or a sub-investigator about the scope and the goals of this trial on the basis of the study-specific patient information leaflet and are then invited to participate. Any study-related measure (including diagnostic screening procedures) will only take place after the patient has personally signed and dated the study-specific informed consent form. Patients will have at least 24 hours to consider their participation in this trial before signing the informed consent form.

### Randomization procedure

The randomization will be performed with the clinical database software secuTrial that is also used for the data management in the study. The two arms will be randomized in a 1:1 ratio using the minimization method described by Pocock and Simon with a stratification for age and gender.

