## Methods and design

RiMINI is a monocentric exploratory pilot study on 60 patients with MHE as assessed by critical flicker frequency (CFF) analysis. Additionally, visual evoked potentials’ (VEP) testing, electroencephalography (EEG) and a psychometric test (NCT-A) will be carried out. The patients will be randomized to treatment either with rifaximin alone 550 mg twice daily (bid) continuously for a period of 3 months or to continuous treatment with 550 mg rifaximin bid in combination with lactulose 30–60 ml daily (to pass 2–3 semisoft stools/day) for 3 months. An esophagogastroduodenoscopy (EGD) will be performed at baseline, at the end of antibiotic treatment, as well as 6 and 12 weeks after the end of treatment to obtain gastric and duodenal biopsies and aspirates will be taken. The samples will be analyzed for their specific bacterial taxae by applying next generation sequencing (NGS) after ribonucleic acid (RNA) isolation. Additionally, stool samples will be taken at the same time points. Prevalence of *Helicobacter pylori*, which is the predominant gastric microbe, will be assessed by histology, rapid urease test and serology at study entry. For clinical assessment, quantification of MHE and therapeutic effects, CFF, EEG, VEP and psychometric tests are assessed weekly during the first month and every 4 weeks from the beginning of the second month until the end of the post-treatment follow-up.

Changes in the gut microbiome from antibiotic therapy with rifaximin alone or rifaximin with lactulose are analyzed comparing pre- and post-antibiotic time points. The follow-up data will show whether the change in the gut microbiome is persistent or transient. We will compare the effect of antibiotic therapy with rifaximin alone with a combination therapy with lactulose on the clinical course of MHE. As planned, NGS methods (Illumina sequencing, Illumina, San Diego, CA, USA) will be used to characterize the composition and changes of both stomach and small bowel microbiomes. Bacterial ribosomal ribonucleic acid (rRNA) will be isolated from aspirates, biopsies and feces and then stored in RNAlater at −80 °C. The samples will be analyzed by NGS methods as described below with the aim of identifying the microbiome of the stomach and the small bowel, as well as of the large bowel, in patients with liver cirrhosis and MHE and its changes before and after therapy (Fig. 1).

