### All subjects

Men and women in the age range 18–90 years at the time of enrollment and who are mentally competent, willing and able to understand the nature and risks of the proposed study, and able to sign the consent form prior to study entry. The individuals must have a projected life expectancy of 6 months or longer and must be able to comply with all study procedures and requirements. Women with childbearing potential must have a negative pregnancy test during the screening period. The diagnosis of liver cirrhosis is needed, established either by histology or by typical signs on transabdominal ultrasound in combination with signs of portal hypertension (ascites, enlarged spleen, fundic or esophageal varices), and the presence of MHE has to be confirmed. To confirm the diagnosis of MHE the following tests will be performed: number-connection test A (NCT-A), critical flicker frequency analysis (CFF), electroencephalography (EEG), and visual evoked potentials (VEP) whereby the final confirmation of MHE depends on the CFF result (CFF <39 Hz). The additional neurophysiological and neuropsychometric tests will be analyzed concerning diagnostic utility alone or in combination.

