### Statistical analysis

All demographic and baseline variables are presented in descriptive statistics stratified by treatment arm in the full analysis set (FAS, all randomized patients). Exploratory tests, according to the level of the respective variables, will search for differences between both arms which might occur despite randomization. The primary target variable is compared between both treatment arms. The odds ratio for treatment success is calculated between both treatment arms together with the corresponding two-sided 95 % confidence interval. If the confidence interval is completely above or below the threshold of 1, the superiority of the corresponding treatment arm with larger success rates can be concluded. If the confidence interval covers the threshold of 1, then the lower and upper confidence limits give limits which can be used in non-inferiority statements. This analysis is performed primarily in the modified full analysis set (MFAS, all randomized patients but excluding those with missing CFF tests) according to the ITT principle. Missing values are imputed by the last observation carried forward principle.

Secondary analyses for the primary target variable include (1) logistic regression analysis with treatment arm, sex, age and baseline value of CFF as co-variables, (2) analog analyses in the per protocol set (PPS, patients of the MFAS excluding those with severe protocol violations), (3) analog analyses for the result of CFF at end of follow-up, (4) description of the results of the psychometric tests (mean and standard deviation) per treatment arm and comparison in two-sample *t* tests (both at end of treatment and end of follow-up).

The secondary efficacy variables are compared between the treatment arms in analysis of covariance (ANCOVA) models with treatment arm, sex, age and respective baseline variable as factors or co-variables, respectively.

Safety analysis is done in the safety set (SS, patients receiving at least one treatment) in descriptive and exploratory analyses. Laboratory variables and rates of SAEs are compared between both treatment arms using the Mann-Whitney *U* test and Fisher’s exact test.

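### The primary odds ratio ignores screening CFF, which the minimization also leaves out; the CFF-adjusted model that the plan already contains should be primary, not secondary

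*Protocol article*

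**What the plan says.** **Allocation.** The Protocol article, Randomization procedure, sets equal allocation to two arms by Pocock-Simon minimization, "with a stratification for age and gender". CFF is not a factor.

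**CFF at entry.** Under All subjects, four tests are done, "whereby the final confirmation of MHE depends on the CFF result", with a cut-off of 39 Hz. Table 1 places the row "Assessment of neurocognitive function (NCT-A, CFF, VEP, EEG") at screening, ahead of assignment at visit 0. Every patient's value is therefore on record when the arm is assigned.

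**Primary analysis.** Under Statistical analysis: "The odds ratio for treatment success is calculated between both treatment arms", with a two-sided 95% confidence interval set against 1. No covariate is named. The article does not spell out treatment success. That it is CFF-based is inferred from two statements in the same section: the primary analysis set leaves out patients without CFF tests, and one secondary analysis repeats the comparison for CFF at the end of follow-up.

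**Secondary analysis.** The first one listed for the same variable is "logistic regression analysis with treatment arm, sex, age and baseline value of CFF as co-variables". Exploratory tests for baseline differences between the arms are also planned.

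**Size and status.** Methods and design: "RiMINI is a monocentric exploratory pilot study on 60 patients with MHE". The Power analysis section says that the results will serve to plan a confirmatory trial.

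**The concern.** By listing baseline CFF in its own model, the plan treats it as prognostic. Yet neither the allocation nor the primary estimate takes account of it. If success depends on where a patient starts, a chance difference in screening CFF between two arms of 30 enters the headline odds ratio. It could look like an effect of lactulose or hide one.

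The same interval is meant to support superiority or, failing that, non-inferiority statements, and the estimate feeds the planning of the next trial. What is at stake is how well this one trial's estimate can be trusted, and how much information 60 patients yield.

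**Working it through.** **Inputs from the article.** 60 patients, 1:1, so 30 per arm; odds ratio with two-sided 95% CI.

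**Assumptions, not in the article.** Baseline CFF is measured in SD units. Its association with success is set either at an odds ratio of 1.5, 2 or 3 per SD, or at a baseline-outcome correlation of 0.5 to 0.7. Success is about 50% in the null scenarios. The minimization runs use an assignment probability of 0.8.

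**1. The plan's own figure.** The 60 comes without success rates, power or margin, so it cannot be reproduced. As a consistency check, 30 per arm gives 80% power for 30% v 66% (OR 4.5), 40% v 76% (OR 4.8) or 50% v 84% (OR 5.3). This agrees with the Power analysis section, which expects proof only for a very large effect.

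**2. How often the arms differ.** If allocation is unrelated to CFF, the standardized difference has SD √(2/30) = 0.258.
- P(|d| ≥ 0.25) = 2[1 − Φ(0.25/0.258)] = 33%
- P(|d| ≥ 0.5) = 2[1 − Φ(0.5/0.258)] = 5.3%

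Simulated minimization on age and gender gives 33-35% and 5-7%. With CFF in three classes as a third factor it gives 11-12% and under 1%.

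**3. What a 0.5 SD difference does to a null odds ratio.**

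| Assumed association | Average unadjusted OR |
|---|---|
| OR 1.5 per SD | 1.19 |
| OR 2 per SD | 1.35 |
| OR 3 per SD | 1.55 |
| Correlation 0.5 | about 1.5 |
| Correlation 0.7 | about 1.75 |

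For scale, at 50% success the standard error of the log odds ratio is √(4/15) = 0.516. Since ln 1.2 = 0.18 and ln 1.75 = 0.56, the shift is 0.18/0.516 = 0.35 to 0.56/0.516 = 1.08 standard errors.

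**4. Type I error without CFF balancing** (8,000 runs each).

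| OR per SD | Unadjusted, all trials | Unadjusted, difference ≥ 0.5 SD | CFF-adjusted, difference ≥ 0.5 SD |
|---|---|---|---|
| 1.5 | 5.4% | 6.6% | 5.4% |
| 2 | 5.6% | 14.4% | 6.4% |
| 3 | 5.2% | 15.1% | 3.8% |

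The last two columns rest on about 5% of the runs, roughly 400 trials, and are correspondingly rough.

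**5. Power at a conditional treatment odds ratio of 4** (4,000 runs each).

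| OR per SD | Unadjusted | Adjusted | CFF-balanced, unadjusted | CFF-balanced, adjusted |
|---|---|---|---|---|
| 1.5 | 0.72 | 0.72 | 0.72 | 0.73 |
| 2 | 0.69 | 0.71 | 0.70 | 0.72 |
| 3 | 0.58 | 0.63 | 0.57 | 0.63 |

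The adjusted model in steps 4 and 5 contained treatment and CFF only. Repeating the null runs with sex and age added left the error rate at its nominal level.

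At a correlation of 0.5 to 0.7, adjustment with allocation unchanged raises power from about 0.65 to 0.70-0.76. Balancing without adjustment gives 0.62, with type I error of 0.03-0.04. In runs with a larger effect, balancing alone moved power from 79.5% to 80.6% (correlation 0.5) and from 78.6% to 82.0% (0.7). Adjustment alone gave 83.4% and 90.0%, and both together 84.7% and 90.9%.

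**6. Why balancing alone does not pay.** It narrows the true spread of the log odds ratio, but the unadjusted Wald standard error does not register this: its mean was 0.526 without and 0.525 with three CFF classes. The interval stays as wide as before and becomes conservative.

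**The case against.** Minimizing on two factors in a 60-patient pilot is a legitimate choice, and the confidence interval already allows for chance imbalance. The plan looks for baseline differences and fits a CFF-adjusted model, so an imbalance would be seen and corrected. The strength of the association is assumed, and the entry ceiling of 39 Hz may narrow the spread in Hz. The article condenses a fuller protocol, so the missing definition of success is no fault here.

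All of this stands. It limits the point to the ranking of two analyses that the article itself fixes.

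Two stronger readings are tempting:
- **That omitting CFF from the minimization biases the trial.** Step 4 contradicts this: error over all randomizations is nominal. The raised rates belong to the few trials with a large imbalance.
- **That balancing on CFF is worth extra patients.** Step 6 shows that the planned analysis cannot collect that gain. Power changed by between about −3 and +3 percentage points.

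What the objection does not answer is that the headline figure remains the unadjusted one. Baseline tests reveal an imbalance but do not remove it, and choosing which odds ratio to believe after seeing both is weaker than fixing the choice beforehand.

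**Conclusion.** The point holds as a modest improvement in efficiency and robustness, not as an error or contradiction. A 0.5 SD imbalance occurs in about 1 trial in 20 and moves a null odds ratio to about 1.2 to 1.75. Adjustment corrects this. It adds about 5 to 11 points of power at correlations of 0.5 to 0.7, but almost nothing if the association is as weak as an odds ratio of 1.5 per SD. It needs only data and a model already in the plan.

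The sizes rest on the assumed association, success rates and treatment effect. The point itself also rests on the inference that success is CFF-based. The pilot status lowers the stakes, although the estimate is meant to inform the next trial.

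**What to change.** **Main change.** By dated amendment, before outcomes are compared by arm, make the planned logistic regression with treatment arm, sex, age and continuous baseline CFF the primary analysis. Report the unadjusted odds ratio as supportive. This also brings the two minimization factors into the primary model.

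**Cost.** No new data are needed. The adjusted odds ratio is conditional on the covariates, generally lies further from 1 than the unadjusted one, and must be labelled so, especially when it is used to plan the confirmatory trial. The model has four coefficients. At 50% success there are 30 successes, or 30/4 = 7.5 per coefficient, so a penalized-likelihood fallback should be named in case of separation.

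**Optional extra.** For the remaining allocations, add screening CFF in two or three prespecified classes below 39 Hz as a third minimization factor in secuTrial, counting patients already randomized by their recorded values. This reduces chance imbalance but does not replace adjustment. The costs are slightly looser balance on age and gender, a rule change during recruitment (the first patient was randomized on 24 April 2015), and a benefit that shrinks with every patient already allocated. If allocation can no longer be changed, the main change is sufficient.

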### Blinding

Due to the study concept (pills versus pills + liquids) a (double-)blinded concept appeared inoperable: therefore, the study will be performed as an open label study. The use of objective neuropsychometric measurements without learning curves ensures a maximum decrease of confounding effects.

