### Primary objective

This study primarily aims at the analysis of the efficacy of MHE therapy with rifaximin alone or in combination with lactulose on the improvement of neuropsychometric and neurophysiological changes.

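### Tests without learning curves do not protect an open-label comparison from knowledge of the arm, and the Blinding section names no masking of those who run or read the tests

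*Protocol article*

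**What the plan says.** The Blinding section of the protocol article gives one reason for not blinding, that the regimens look different (pills against pills plus liquid), and concludes that "a (double-)blinded concept appeared inoperable: therefore, the study will be performed as an open label study". The safeguard it offers follows at once: "The use of objective neuropsychometric measurements without learning curves ensures a maximum decrease of confounding effects". It says nothing about who runs or reads the tests, or whether they know the arm.

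The tests in question carry the main aim of the trial. The Primary objective section names the "efficacy of MHE therapy with rifaximin alone or in combination with lactulose on the improvement of neuropsychometric and neurophysiological changes". Under Methods and design, "CFF, EEG, VEP and psychometric tests are assessed weekly during the first month and every 4 weeks from the beginning of the second month", and the same schedule applies to both arms. Under Statistical analysis, "The odds ratio for treatment success is calculated between both treatment arms together with the corresponding two-sided 95 % confidence interval", and superiority may be concluded if that interval excludes 1.

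**The concern.** Two steps in the Blinding section do not hold together.

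First, the safeguard answers a different threat. A learning curve makes scores drift upward with repeated testing. With randomised arms and a common schedule, the drift is broadly equal in both arms and mostly cancels in the contrast. What an open-label design adds is the chance that a patient, tester or reader behaves differently by arm. Absence of a learning curve has no bearing on that.

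Second, the obstacle is narrower than the conclusion. A visible difference in treatment explains why patients and the staff who handle treatment cannot be masked. It does not explain why a person operating the flicker test, timing the number-connection test or reading a stored EEG or VEP trace would have to know the arm.

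At stake is the between-arm odds ratio. The Power analysis section says the results will be the basis for planning a confirmatory multicentre trial, so a biased contrast would be carried into that design.

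**Working it through.** **Reasoning from the text.** The claim under review contains no figure, so there is none to reproduce. Set side by side:

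| Element in the Blinding section | Threat it bears on | Effect on the between-arm contrast |
|---|---|---|
| No learning curves | Practice effects | Little: broadly shared by both arms |
| Objective measurements | Tester or reader influence | Reduces it, does not remove it |
| Regimens look different | Masking of patients and treating staff | Does not bar masking of testers or readers |

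On the second row, NCT-A is a psychometric performance test, and EEG and VEP have to be read. The sentence also speaks only of neuropsychometric measurements, while the primary objective covers neurophysiological changes too.

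**Illustration of size.** Inputs from the document:
- 60 patients (Methods and design) and 1:1 allocation (Randomization procedure), hence about 30 per arm.
- Two-sided 95% interval for the odds ratio (Statistical analysis).
- MHE confirmed by CFF below 39 Hz (All subjects).

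Inputs assumed, because the document gives none of them:
- Success means CFF at or above a cut at end of treatment.
- No true treatment effect, and 50% success in the unshifted arm.
- SD of end-of-treatment CFF 2 to 3 Hz.
- A differential shift of 0.5 to 1 Hz caused by knowledge of the arm.

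Success in the shifted arm is Φ(shift / SD). The chance that a Wald interval for the odds ratio excludes 1 comes from exact enumeration of two binomial arms of 30, adding 0.5 to each cell when a cell is zero.

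| Shift | SD | Success in shifted arm | Interval excludes 1 |
|---|---|---|---|
| 0 | either | 50% | 5.2% |
| 0.5 Hz | 3 Hz | Φ(0.167) = 56.6% | 8.3% |
| 0.5 Hz | 2 Hz | Φ(0.25) = 59.9% | 12.1% |
| 1 Hz | 3 Hz | Φ(0.333) = 63.1% | 17.5% |
| 1 Hz | 2 Hz | Φ(0.5) = 69.1% | 32.2% |

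The same calculation without any assumption about Hz, with the shift stated directly in points of recorded success and true success set at 30%, 50% or 60%:

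| Shift in recorded success | Interval excludes 1 | Spurious odds ratio |
|---|---|---|
| 0 points | 4.1 to 5.2% | 1.0 |
| 5 points | 6.0 to 6.9% | 1.22 to 1.26 |
| 10 points | 11.6 to 12.3% | 1.50 to 1.56 |
| 15 points | 21.3 to 21.6% | 1.86 to 2.00 |
| 20 points | 34.7 to 36.5% | 2.33 to 2.67 |

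A practice effect equal in both arms is the zero row only, which is why freedom from learning curves changes little here.

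**The case against.** The strongest reply is that the sentence relies on objectivity as well as on the absence of learning curves, and objectivity does limit what an informed tester can change. That stands in part: it supports saying that detection bias is reduced, but not that its maximum decrease is ensured.

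Learning curves are not irrelevant either. Under repeated testing they would confound change over time within an arm, so their absence helps any before-and-after reading. It does not help the contrast between arms.

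A reader might infer that masked assessment was considered and rejected, or that testers do know the arm. The document does not support this. It is a condensed article, it does not say who tests or reads, and the full protocol may name masked assessors. What can be said is that a section devoted to blinding states its safeguard and lists no masking. If the masking exists, it need only be stated.

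A reader might also infer that patients start just under the CFF cut, so that a trivial shift reclassifies many of them. The eligibility text requires only a value below 39 Hz, with no lower bound and no baseline distribution.

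Finally, masked assessors would not remove bias from patients who know their arm and may perform differently. Masked reading of EEG and VEP would not touch the primary comparison if success is CFF-based, as the analysis set that excludes missing CFF tests suggests. Both limits stand.

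**Conclusion.** The point holds as an overstated safeguard and a missed low-cost measure. Freedom from learning curves does not protect the odds-ratio comparison from knowledge of allocation, objectivity protects it only partly, and the reason given for going open label does not rule out masking testers and readers.

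Its size is unknown. The range of about 8 to 32% for false superiority shows what a differential shift would do if it occurred. It is not an estimate of what will occur, because the shift, the SD, the success rate and the definition of treatment success are all absent from the document. The 50% rate is also where a given shift in Hz moves the success rate most. Nothing here shows that CFF is in fact biased, and the figures should not be read as the trial's false-positive rate.

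The trial is described as exploratory: "RiMINI is a monocentric exploratory pilot study on 60 patients with MHE as assessed by critical flicker frequency (CFF) analysis". That lowers the weight of the point. It remains worth acting on because a superiority conclusion is allowed and the results feed a later trial.

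**What to change.** - Store EEG and VEP recordings under a code and have them read without arm information.
- Where existing staffing allows, have CFF and NCT-A run by staff who are not told the arm and do not handle study medication.
- Record any unmasking of a tester or reader.
- Replace the sentence that claims a maximum decrease of confounding with a statement that assessor masking and objective tests reduce detection bias, while bias from unmasked patients remains.

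No visit, test or patient is added. The cost is coded file names, some rota constraints at a single centre, and occasional unmasking when a patient mentions the treatment. Because the document does not say who performs these tasks, the sponsor must confirm that present staffing permits the separation. The Trial status section reports that recruitment is under way, so the change would apply to remaining assessments and to stored recordings not yet read. If the full protocol already provides for masked assessment, stating it and correcting the sentence is enough.
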